**Methods and analysis:**

This assessor-blinded, parallel group randomised controlled trial is comparing the efficacy of walk-and-talk therapy to conventional indoor therapy for men with depressive symptoms. After randomisation, all participants receive 10 fortnightly 1-hour individual psychotherapy sessions over 20 weeks as either: (1) conventional indoor therapy (sitting down indoors) or (2) walk-and-talk therapy (walking outdoors). Participants are assessed at ‘pre-intervention’ (baseline), ‘post-intervention’ (5 months post baseline) and ‘follow-up’ (12 months post baseline) time points. The primary outcome is change in overall psychological distress (21-item version of the Depression, Anxiety and Stress Scale (DASS-21)) at post-intervention. Secondary outcomes include male-type depression symptoms, mental well-being, suicidal ideation and quality of life. Costing data is being collected for cost-effectiveness analysis. Linear mixed models will be used to examine the impact of group (conventional indoor vs walk-and-talk), time (baseline, 5-month and 12-month) and the group-by-time interaction for primary and secondary outcomes.

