#### Randomisation and allocation

Within each cohort, randomisation occurred after all participants had completed their baseline assessment and had been scheduled for a recurring fortnightly session time. At this stage, the trial coordinator sent a blinded version of the schedule (with no participant names) to a university staff member who was not affiliated with the trial. The external staff member then generated the randomisation sequences using the online Sealed Envelope randomisation tool and allocated the therapy timeslots to either ‘conventional indoor therapy’ or ‘walk-and-talk therapy’ according to this sequence. To ensure each psychologist received an equal share of participants from both groups, but no more than three walk-and-talk sessions on their typical workday, the schedule was stratified by psychologist and blocked in groups of four in a 1:1 ratio. Allocation concealment was maintained throughout enrolment and baseline data collection: eligibility was determined by the research team based on completion of an online screener, after which eligible participants were emailed a baseline survey preceded by the study consent form (see online supplemental material). Because randomisation did not occur until all baseline data had been collected within a cohort, the research team had no access to allocation sequences during this period. After generating the randomisation sequence, the external staff member emailed the completed schedule to the trial coordinator, who informed participants about their condition assignment prior to the first scheduled session.

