### Measures

Participants completed three online surveys (baseline, post-intervention at 5 months and 12-month follow-up) via QuestionPro, a secure online survey platform licensed by the University of Newcastle. The baseline survey was completed after all participants were enrolled and prior to their first therapy session. The post-intervention survey was completed approximately 1 week after their last therapy session (which was at 5 months post baseline), and the follow-up survey will be completed at 12 months post baseline. Participants will receive an email containing a personalised survey link at each time point. To promote retention and maximise completions at post-study and follow-up, participants who have not responded within 1 week will receive a reminder email, followed by a reminder telephone call and text message if needed. Participants who remain unresponsive will be sent an abbreviated survey containing the primary outcome measure only (DASS-21), consistent with an intention-to-treat approach. At the end of each week, survey data will be exported from QuestionPro and imported into a password-protected database stored on a secure University of Newcastle OneDrive server. All identifying information will be replaced with a unique numerical participant code prior to analysis; however, a separate password-protected linkage file will be retained by the research team to enable longitudinal data linkage across time points. Only members of the research team will have access to identifiable data.

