#### Primary outcome

##### Psychological distress

Overall psychological distress was assessed using the composite score of the DASS-21 measure.^41^ The DASS-21 is a widely used and extensively validated measure of commonly experienced symptoms associated with depression, anxiety and stress over the previous week. Participants rated each item on a 4-point scale ranging from 0 (did not apply to me) to 3 (applied to me very much). To allow for comparison with the original DASS-42 scale, total scores were calculated and then doubled as recommended, with higher scores indicating worse mental health.

Although men with depressive symptoms are the target sample, the primary outcome was informed by pilot trial data, which showed comparable reductions in depressive symptoms across conditions but a potential signal favouring walk-and-talk therapy on overall psychological distress. Given anxiety and stress commonly co-occur with depression,^42^ the current trial was designed to provide an adequately powered test of this preliminary effect on overall distress, which also has a theoretical basis given the established links between physical activity,^43^ nature exposure^44^ and symptoms of depression, anxiety and stress.^45
46^

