Emotional control	Conformity to Masculine Norms-46 (CMNI-46): Emotional Control subscale	^ 62 ^	6	I hate it when people ask me to talk about my feelings	4-point scale: Strongly disagree (1) to strongly agree (4)	X		
Nature connection	Connection with Nature Instrument (CN-12)	^ 63 ^	12	I feel right at home when I am in nature	7-point scale: Strongly disagree (1) to strongly agree (7)	X	X	
Nature contact	Nature Contact	^ 64 ^	1	Over the past month, approximately how many hours per week on average would you consider yourself to have interacted with nature? For example, walking outside, biking, gardening, playing games/sports, camping, fishing, reading outside, yard work, hanging out in a park, etc	Open response	X	X	
Other measures								
Therapy expectancies and preferences	Treatment Acceptability Preferences Scale (TAPS): Expectancies	^ 65 ^	8	How effective do you think this approach would be for improving your mood?	5-point scale: Not at all (0) to very much (4)	X		
	Treatment Acceptability Preferences Scale (TAPS): Preference		1	Do you have a preference for one of the two approaches to therapy?	No; yes - outdoor walk-and-talk; yes - conventional indoor	X		
Therapeutic process indicators	Individual Therapy Process Questionnaire (ITPQ): Global Alliance and Patient Fear subscales	^ 66 ^	5	Today, I felt comfortable in the relationship with the therapist (Global Alliance) Today, it was difficult for me to talk openly with the therapist (Patient Fear)	5-point scale: Does not apply (0) to fully applies (4)	*		

* Measure completed via texted survey after participants’ first, middle and final session.

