### Statistical methods

#### Primary analysis plan

Linear mixed models will examine the primary and secondary outcomes for the impact of group, time (categorical) and the group-by-time interaction. This approach ensures outcomes for participants lost to follow-up are modelled in the analyses, consistent with an intention-to-treat approach. To adjust for potential baseline differences, age, socio-economic status, baseline physical health (Short Form-12 survey (SF-12) physical subscale) and baseline depression treatment (ie, concurrent use of antidepressant medication and/or external psychotherapy) will be examined to determine whether they contribute significantly to the models. If a covariate is significant, a term will be added to the model to adjust for the effects and two-way interactions with time and treatment will also be examined. If these interactions are significant, they will also be adjusted for. For the primary outcome, we will conduct a sensitivity analysis to explore the impact of adjusting for participants’ prerandomisation treatment expectancies (for the arm they were subsequently randomised to) on the group-by-time intervention effect. A post-hoc sensitivity analysis will also be conducted to account for therapist-level clustering by modelling therapist as a random intercept term, enabling direct comparison of results with and without this effect.

As the analyses of secondary outcomes are intended to complement the primary outcome data and provide preliminary insights for future hypothesis testing, no multiplicity adjustments will be conducted. Given the exploratory nature of these secondary analyses, p values <0.05 will be interpreted as suggestive, rather than significant effects for these outcomes. Effect sizes will be calculated using Cohen’s *d* and interpreted as small (*d*=0.2), medium (*d*=0.5) or large (*d*=0.8).^48^

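### The assessor-blinded label does not fit a self-rated primary outcome, and adjusting for expectancy of the allocated arm cannot by itself separate expectancy bias from prognosis

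*Protocol article*

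**What the plan says.** **Blinding.** Abstract, Methods and analysis: "This assessor-blinded, parallel group randomised controlled trial is comparing the efficacy of walk-and-talk therapy to conventional indoor therapy". Measures: "Participants completed three online surveys (baseline, post-intervention at 5 months and 12-month follow-up) via QuestionPro". Psychological distress (the primary outcome): "Participants rated each item on a 4-point scale ranging from 0 (did not apply to me) to 3 (applied to me very much"). The shortened survey for non-responders is the same self-rated scale. Under Randomisation and allocation, the schedule goes to the trial coordinator, "who informed participants about their condition assignment prior to the first scheduled session". The limitations in the summary box and the Discussion cover psychologist self-report, therapist allegiance, clustering and self-selection. They do not mention that the primary outcome is rated by unblinded participants.

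**Expectancy.** Table 1 lists a baseline expectancy scale (example item "How effective do you think this approach would be for improving your mood") and a preference item ("Do you have a preference for one of the two approaches to therapy"). The Primary analysis plan has one analysis that uses expectancy, a sensitivity analysis of the primary outcome that examines the effect of adjusting for "prerandomisation treatment expectancies (for the arm they were subsequently randomised to) on the group-by-time intervention effect".

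**The concern.** A reader who sees assessor-blinded expects outcome ratings to be protected from knowledge of the arm. Here the rater of the primary outcome is the participant, and walking outdoors cannot be masked from sitting indoors. Expectancy and reporting bias are therefore the main threats to the comparison, and the expectancy sensitivity analysis is the article's only stated check on them.

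That check uses a variable that is not an ordinary baseline covariate. Both ratings precede randomisation, but allocation decides which one enters the model. If men rate one format higher on average, the covariate differs between arms by design, and adjusting for it moves the group effect whether or not expectancy caused any bias. A smaller effect could then be reported as explained by expectancy, or a larger one as robust to it, without either being shown.

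**Working it through.** **1. Blinding.** No arithmetic applies. The rater is the participant (Measures; Psychological distress) and knows his arm before session 1 (Randomisation and allocation). Step counts are logged by participants (Physical activity), and unwanted events are rated by the treating psychologist (Unwanted intervention-related events). Interim data were withheld from investigators (Patient and public involvement), but that is not assessor blinding. Nothing in the methods corresponds to the label for the primary outcome.

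**2. Planning figures.** Sample size gives a difference of 8, SD of change 15, alpha 0.05 and 80% power. n = 2 × (1.96 + 0.84)² × 15² / 8² ≈ 55.1, rounded up to 56 per group, as stated (two-sided). 56 / 0.75 = 74.7, rounded up to 75 per group, also as stated. The values 8, 15 and 56 are used below.

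**3. The covariate.** Let Z = 1 for walk-and-talk, and let W and I be a man's baseline ratings of walking and indoor therapy, each with SD 1. Write g for the mean of W minus the mean of I, and r for their correlation. The planned covariate is X = Z·W + (1 − Z)·I. Its expected difference between arms is g, not zero. A positive effect means a greater reduction with walk-and-talk.

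Assumptions not in the documents: r = 0.4, g = ±0.5 SD, and expectancy worth b = 3 or 5 DASS-21 points per SD unit of rating.

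**4. Case A: expectancy marks general prognosis only.** Outcome depends on the mean rating M = (W + I)/2, with no expectancy bias. The slope on X within arms is b(1 + r)/2, so the adjusted effect is 8 − b·g·(1 + r)/2.
- g = +0.5: 8 − 3 × 0.5 × 0.7 = 6.95; 8 − 5 × 0.5 × 0.7 = 6.25.
- g = −0.5: 8 + 1.05 = 9.05; 8 + 1.75 = 9.75.

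The unadjusted effect is 8 in each.

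**5. Case B: outcome depends linearly on the rating of the arm received.** The unadjusted effect is 8 + b·g. Adjusting for X returns 8.
- g = +0.5: unadjusted 8 + 1.5 = 9.5 and 8 + 2.5 = 10.5.
- g = −0.5: unadjusted 6.5 and 5.5.

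**6. Models using both ratings.** Randomisation balances W and I across arms. Entering both as main effects therefore leaves the group effect, on average, where the unadjusted analysis puts it: 8 in Case A, but 9.5 to 10.5 in Case B at g = +0.5. That is no check on expectancy bias. Now let D = W − I. Since X = M + (Z − ½)·D, a model with Z, M, D and Z·D contains both cases, and its group effect at D = 0 is 8 in each.

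| g = +0.5, b = 3 / 5 | Unadjusted | Received-arm rating | Both, main effects | Group effect at D = 0 |
|---|---|---|---|---|
| Case A | 8 / 8 | 6.95 / 6.25 | 8 / 8 | 8 / 8 |
| Case B | 9.5 / 10.5 | 8 / 8 | 9.5 / 10.5 | 8 / 8 |

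Simulation with 56 per arm and SD 15 agrees: Case A about 7.0 to 6.2 (walking favoured) or 9.0 to 9.7 (indoor favoured) under the planned adjustment, and about 8 at D = 0 in both cases. The standard error at D = 0 was about 7 to 17% larger than under the planned adjustment at gaps of 0.5 to 0.8 SD. With r = 0.5, power at D = 0 for a true 8 was about 71 to 75% at a 0.5 SD gap and 52 to 55% at 1 SD. When g = 0, all models agree.

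**The case against.** The planned analysis is not simply wrong. In Case B, the situation it is meant for, it recovers the true effect while the unadjusted estimate does not. A reader might infer from Case A that it should be dropped; the documents do not support that, because nothing in them says which case applies. It is also a declared sensitivity analysis with no decision rule.

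The rating gap, its direction and the correlation appear nowhere in the article. Every man had to be willing to accept either arm, which may keep the gap small, and with no gap there is no shift. All of this stands, and it limits the size of the point. It does not remove it: the article expects walking to suit men's preferences better, so a gap is plausible, and the planned covariate alone cannot show which case holds.

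A reader might also infer that the expectancy term, if constant over time, would cancel out of the group-by-time effect and leave the analysis empty. The article does not say it enters that way. It states the target as the group-by-time effect and examines time interactions for other covariates, and the exact form may be settled in an analysis plan not shown.

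On blinding, the label may refer to staff or analysts. The article claims no participant blinding and discloses allocation openly. So the text does not show that nobody was blinded, only that the label does not fit the primary outcome as described.

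**Conclusion.** Both parts hold, at moderate weight. The label is at odds with the article's own methods for the primary outcome. The expectancy adjustment gives the right answer under one assumption and a biased one, in either direction, under another: shifts of about 1.0 to 1.8 units on a true 8 at an assumed 0.5 SD gap. That each man rated both formats is inferred from the baseline-only collection and from the covariate's definition, which requires it.

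A reader might conclude that the trial's main result is compromised. It is not: the primary analysis does not use this covariate. The effect at difference zero has limits too. It assumes linear relations, it would also absorb a genuinely larger benefit in men who prefer walking, and no pre-randomisation rating captures disappointment after allocation is disclosed.

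**What to change.** 1. In the abstract, describe the primary outcome as participant-reported and unblinded, or state who was blinded to what. Add unblinded self-report to the limitations in the summary box and the Discussion.
2. Keep the received-arm analysis. Alongside it, fit the mixed model with the mean of the two pre-randomisation ratings and their walk-minus-indoor difference, each interacted with time, plus group-by-difference at 5 months. Report the group effect at difference zero, not at the average difference, together with the observed mean gap and the correlation of the ratings.
3. State that a change under the received-arm adjustment alone will not be read as explained by expectancy, and that entering both ratings as main effects only is not a check.

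**Cost.** No new data if both ratings were collected as inferred. Precision at difference zero is lower, as shown above, and the blinding description becomes less favourable. Post-intervention assessments are complete in all three cohorts, so the added model must be declared as added after that data collection.

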## Methods

### Study design

The study design is a parallel-group superiority randomised trial repeated across three cohorts. In each cohort, participants are assessed at baseline, 5 months (post-intervention) and 12 months (follow-up). After completing baseline measures, participants were randomly allocated to either conventional indoor therapy (sitting down indoors) or walk-and-talk therapy (walking outdoors). At the time of writing, recruitment, intervention delivery and post-intervention assessments have been completed across all three cohorts, with 12-month follow-up assessments currently underway. The study was approved by the University of Newcastle Human Research Ethics Committee (HREC) (H-2024-0090) and was prospectively registered with the Australian New Zealand Clinical Trials Registry (ACTRN12624000794505, ANZCTR - Registration, 27 June 2024). Any modifications to the study protocol would be submitted to HREC for approval prior to implementation and updated in the publicly available trial registry. No substantial protocol amendments have been made up to this point. All participants receive $A10 vouchers for completing the post-intervention survey at 5 months and follow-up survey at 12 months ($A20 in total). The reporting of this study will adhere to the Consolidated Standards of Reporting Trials (CONSORT) guidelines.^34^

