#### Interventions

In both conditions, participants were invited to attend 10 fortnightly 60-minute individual psychotherapy sessions over 20 weeks. Participants were scheduled to attend one session per fortnight on the same day and time, with the same psychologist and within their allocated condition. If a participant missed a session, they were offered the opportunity to reschedule with the same psychologist within a time slot allocated to their assigned treatment condition, pending psychologist availability. There was no cost to participants for the sessions.

The sessions were delivered by provisionally registered (n=1) or registered (n=12) psychologists. The provisional psychologist received weekly supervision from a senior registered clinical psychologist during the trial. To prevent confounding, all psychologists delivered therapy in both study arms. Members of the research team delivered a half-day training session for the psychologists prior to working with participants, which involved walking the therapy route, contingency planning, strategies for maintaining safety and confidentiality and details on the proposed therapy style.

The sessions involved a non‐directive supportive therapy style using counselling micro‐skills to address important issues identified by the participant.^39^ This approach remained consistent in each study arm and was selected for the current study for several reasons: (1) it could be feasibly delivered in both indoor and outdoor environments (compared with other approaches which require access to worksheets, manuals or other resources), (2) it maintained the focus of the trial on the experimental manipulation (ie, the conventional indoor vs walk-and-talk context), (3) all psychologists in Australia are required to demonstrate competency with this approach during their training and (4) it is effective for treating depression.^39
40^

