Strengths of this study protocol include a randomised design with an active intervention control group (conventional indoor therapy), a preregistered, detailed statistical analysis plan that will follow the intention-to-treat principle and the inclusion of a 12-month follow-up to measure the longer-term treatment outcomes. In addition to measuring overall psychological distress (depression, anxiety and stress), a comprehensive range of secondary outcomes will also be assessed to capture other psychological (male-type depression symptoms, mental well-being, suicidal ideation, quality of life), behavioural (physical activity, sleep, nature contact), social (nature connection, emotional control, engagement in valued activities, mental restoration) and economic (costs) impacts of the programme. By successfully completing this trial, insights into the efficacy of an innovative psychotherapy approach for men will be generated through various analytical methods (eg, mediation and moderation analyses). Lastly, recruitment efforts will focus on men residing in areas identified as socio-economically disadvantaged to ensure a diverse sample. Limitations of the current study include reliance on psychologist self-report to assess adherence to the therapy modality, as sessions are not independently coded. This approach was necessary due to the practical challenges of recording sessions in outdoor settings; however, it may introduce bias into the fidelity assessment. Furthermore, data relating to therapist favourability to a particular therapy setting were not collected, which may represent an additional source of bias; future trials building on this work would benefit from collecting therapist allegiance data to enable assessment of its potential influence in sensitivity analyses. The power calculation did not account for therapist-level clustering; the extent to which this affects statistical power will depend on the magnitude of the therapist-level intraclass correlation coefficient, which will be reported alongside the trial outcomes. In addition, participants self-select into a trial conducted at a university campus, which may limit generalisability to other clinical populations and health service settings. Individuals who are willing to participate in such trials may be more motivated or more receptive to novel therapeutic approaches than the general population. As such, further research will be needed to evaluate this intervention when implemented within routine care contexts.

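### Cohort and psychologist defined the randomisation but are absent from the primary model, and the therapist random-intercept check cannot materially change the 5-month contrast

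*Protocol article*

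**What the plan says.** The protocol article describes a "parallel-group superiority randomised trial repeated across three cohorts". Under Randomisation and allocation it states: "Within each cohort, randomisation occurred after all participants had completed their baseline assessment". It adds that "the schedule was stratified by psychologist and blocked in groups of four in a 1:1 ratio". Cohort and psychologist are therefore both design strata.

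The Interventions section says that therapy was given by "provisionally registered (n=1) or registered (n=12) psychologists", 13 in all, and that "all psychologists delivered therapy in both study arms". Psychologist is thus crossed with arm.

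The Abstract says: "The primary outcome is change in overall psychological distress", assessed post-intervention (5 months). The Primary analysis plan models group, categorical time and their interaction. Age, socio-economic status, SF-12 physical score and baseline depression treatment enter only if significant. Cohort and psychologist are not on that list. Psychologist appears once, in a post-hoc sensitivity analysis intended to "account for therapist-level clustering by modelling therapist as a random intercept term, enabling direct comparison of results with and without this effect".

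The Discussion concedes that the power calculation ignored therapist clustering, and says that "the extent to which this affects statistical power will depend on the magnitude of the therapist-level intraclass correlation coefficient".

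**The concern.** An analysis should normally reflect the factors that restricted the randomisation. If psychologists or cohorts differ in how much their men improve, stratification removes that variation from the treatment comparison. A model without the strata leaves it in the error term, so the SE is too large.

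The second issue is the check itself. A random intercept shifts all of a therapist's patients by the same amount at every visit, including baseline. Baseline was recorded before the first session, so an intercept that spans it does not describe what therapists did to improvement. The treatment effect is a difference in change, and such a shift drops out of it. The comparison with and without the term will therefore agree whatever the therapists' influence on improvement. That includes the one form of therapist variation, by arm, that would make the reported SE too small.

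**Working it through.** **1. The plan's own figure.** Inputs from Sample size: difference 8, SD of change 15, alpha 0.05 (two-sided assumed; it reproduces the figure), power 80%, attrition 25%.

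- n per group = 2 × (1.960 + 0.842)² × 225 / 64 = 55.2, so 56. Then 56 / 0.75 = 74.7, so 75 per group, 150 in total. Reproduced.
- SE = 15 × √(2/56) = 2.835. Power = Φ(8/2.835 − 1.960) = 80.6% (79.9% by the noncentral t).

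**2. What the random intercept does.** Write the score of man *i* with psychologist *k* at visit *t* as fixed effects + u(i) + v(k) + e(it). His change from baseline to 5 months is fixed effects + e(i,5) − e(i,0), so v(k) has gone. Checks with 13 psychologists, 1:1 within psychologist, and variances set to give SD of change 15:

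- Complete data, 150 men: SE of the 5-month contrast = 2.449 at therapist variance 0, 25 and 100. In simulated trials the estimate changed by 0.000. The identity held under compound-symmetric and unstructured participant covariance.
- 25% attrition: raising the therapist variance moved the SE only from 2.859 to 2.863. In simulated trials the estimate moved by 0.02 to 0.05 points on average (largest 0.29 in 40 trials per setting), against a design effect of 8. Cancellation is no longer exact because some men contribute only a baseline score.

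**3. Omitting the strata.** Assume that a share ρ of the change variance lies between psychologists, equally in both arms, with total SD held at 15. Stratified allocation gives a true SE of 2.835 × √(1 − ρ), while a model without strata still reports about 2.835. Normal approximation, 56 per group:

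| ρ | True SE | SE overstated by | Type I error | Power, strata omitted | Power, strata modelled | Points lost |
|---|---|---|---|---|---|---|
| 0.01 | 2.821 | 0.5% | 0.049 | 80.7% | 81.0% | 0.3 |
| 0.05 | 2.763 | 2.6% | 0.044 | 81.2% | 82.5% | 1.3 |
| 0.10 | 2.689 | 5.4% | 0.039 | 81.8% | 84.5% | 2.7 |

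The loss compares the two analyses of the same stratified trial. Comparing with the nominal 80.6% instead would overstate it.

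**4. Therapist-by-arm variation.** Let *s* be the SD across psychologists of the treatment difference. Variance = 4 × 225/112 + s²/13 = 8.036 + s²/13.

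| s (units) | True SE | Excess over 2.835 | Type I error if ignored | Power with the correct SE |
|---|---|---|---|---|
| 1 | 2.848 | 0.5% | 5.1% | 80% |
| 2 | 2.889 | 1.9% | 5.4% | 79% |
| 3 | 2.954 | 4.2% | 6.0% | 77% |
| 5 | 3.156 | 11.3% | 7.8% | 72% |

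**5. Whether the planned check would see it.** A deliberately large case: variance 22.5 in each psychologist-arm cell, so s = √(2 × 22.5) = 6.7, with 150 men and complete data. True SE = √(4 × 225/150 + 45/13) = √9.46 = 3.08. The model SE was 2.45 both without and with the random intercept.

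**The case against.** Several points on the other side are sound.

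- **Validity.** A reader might infer that leaving out the strata inflates false positives. It does the reverse: type I error falls below 5%, and the efficiency loss is small. Time-constant cohort or psychologist main effects also cancel from change, so only their interactions with visit bring a gain. No separate figure can be given for cohort.
- **Therapist-by-arm size.** A reader might infer that the trial's type I error is really 6-8%. Nothing in the article supports a particular value of *s*. An SD of 3-5 is large beside a target of 8, given that the same psychologists use the same therapy style in both arms. At 1-2 units the effect is slight. The inflation also presumes inference to a wider population of therapists; for the average effect among these 13 it does not enter the SE in this way.
- **The Discussion sentence.** A reader might infer that it names the wrong quantity. It does not say whether its ICC concerns level or change. If it means change, a therapist effect common to both arms does bear on precision, as step 3 shows. The sentence is ambiguous rather than wrong.
- **Disclosure.** The article lists therapist clustering as a limitation and calls the check a sensitivity analysis. It nowhere says that agreement will be read as ruling out therapist effects.
- **Unseen analysis plan.** Strata terms and random-effect structure are often left to that document. Here, though, the article itself lists the model terms and candidate covariates and fixes the form of the therapist check, so the point can be judged on what is printed.

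None of this rescues the check. Disclosing clustering does not make a term that cancels from the contrast informative about it.

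**Conclusion.** The point holds in limited form. The primary model omits both randomisation strata, and the single planned therapist analysis is uninformative for the primary contrast. It has exactly no effect with complete data and a negligible one with 25% attrition; to say that it cannot change the result at all would be too strong. The cancellation rests on the model's structure, not on assumed variances.

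The sizes do rest on assumptions, because the article gives no therapist variances. Omitting the strata costs about 0.3 points of power at an ICC of change of 0.01, and about 1.3-2.7 points at 0.05-0.10, on the conservative side. Therapist-by-arm variation with SD 1-5 units would put type I error at 5.1-7.8% and power at about 80-72%, and the planned check would miss it. The sample size of 56 per group, 150 in total, stands.

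**What to change.** - **Primary model:** add psychologist and cohort, each with a visit interaction. If baseline DASS-21 is instead handled as a covariate, main effects suffice.
- **Sensitivity analysis:** replace the random intercept with random psychologist and psychologist-by-group effects on the post-baseline visits, use small-sample degrees of freedom, and report both variances.
- **Discussion:** state that the relevant therapist variance concerns change, and that, with psychologists crossed with arm, it is the psychologist-by-group component that can take power below the stated figure.

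**Cost:** no change to data, conduct or sample size. As fixed effects, the strata use 12 + 2 = 14 main-effect coefficients, and 28 more if interacted with both post-baseline visits. The psychologist-by-group variance will be imprecise with 13 psychologists. The analysis is preregistered and the 5-month assessments are complete, so the change needs a documented update, through the ethics and registry route that the article describes, before the data are analysed. The article says that 12-month follow-up is still underway and that interim data were not made available to investigators.
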